### Intervention

The Guide Cymru is an intervention and resource aimed at improving knowledge and attitudes towards mental health in adolescent populations. It is based on The Guide [25] which was originally written for and tested on 16–17 year olds in North America. The Guide (and therefore The Guide Cymru) includes 6 modules to mental health including; Understanding Mental Health and Mental Illness, Seeking help and the importance of positive mental health. The Guide has evidenced sustained improvements in student’s mental health literacy in Canada [27].

The Guide Cymru was adapted by Action for Children (a UK based charity) via a team that included psychologists, senior teachers, a child psychiatrist, and children (age 14) to be more appropriate for the intended age group (13–14 year olds) and the Welsh setting. After adaptation, all materials were translated into Welsh for delivery in this language if the school wished.

The Guide Cymru includes a two-day training course for teachers (termed the Go-To Educator) that covers the materials in The Guide Cymru and the learning resources available. Each school that signs up to the intervention programme will be invited to send up to three teachers (free of charge) to this training. These teachers will then deliver The Guide Cymru to their students over a next 8–10 weeks.

### Procedure

Data will be collected in three waves.

#### Wave one

The aim of wave one is to provide baseline measures of mental health literacy, and levels of psychological function and mental health difficulties. The wave will occur approximately 1 week prior to these teachers being trained on Go-To Educator and then delivering the intervention programme to their students over the following 10 weeks. A member of our research team will visit each school on the day of testing to help the teachers administer the questionnaires to the students.

For each school in the intervention arm of the RCT there will be a “yoked” school in the wait list control arm and the data from the yoked school will be collected on the same day and in the same manner as the one in the active arm.

We will determine Social Economic Status (SES) and special needs status of the schools through the Welsh Government Annual Documentation detailing a percentage of many pupils are eligible for free school meals and how many require additional learning support.

#### Wave two

The wave will occur approximately 1–2 weeks post the delivery of The Guide Cymru for the students in the intervention arm of the study, with the wait list control yoked schools being tested at the same time.

#### Wave three

Wave three will occur approximately 1–2 weeks post the delivery of The Guide Cymru for the students in the wait list control arm of the study, with the yoked school in the active arm being tested at the same time (which will be approximately 14 weeks after these schools had completed the mental health literacy intervention).

### Secondary outcome measures

#### PedsQL

The Pediatric Quality of life inventory (PedsQL) 4.0 Generic Core Scales [28] is a health-related quality of life measure that has demonstrated good reliability and construct validity in various populations [29]. The PedsQL 4.0 Generic Core Scales instrument consists of the following 4 domains: (1) Physical Functioning, (2) Emotional Functioning, (3) Social Functioning, and (4) School Functioning. It includes format for typically developing children aged 5 to 18 years old. Participants rate each description regarding to their heath over the past month using a five point Likert scale (never, almost never, sometimes, often, almost always). Item scores that then transformed to a score out of 100 with high scores indicating a high quality of life.

#### Strengths and difficulties questionnaire

The Strengths and Difficulties Questionnaire (SDQ) [30] assesses the psychological adjustment of children and youths. The SDQ has 25 items, both positive and negative, answered using a 3-point Likert scale (not true, somewhat true, certainly true) to indicate how far each item applies to the individual over the past 6 months. The 25 items are divided between five scales of five items each, generating scores for emotional symptoms, conduct problems, hyperactivity-inattention, peer problems and prosocial behaviour. Emotional, conduct, hyperactivity- inattention and peer problems are summed to generate a total difficulties score. Higher scores indicate more difficulties. The SDQ has well documented psychometric properties [30].

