**Methods:**

This two-armed cluster randomised control trial (RCT) will evaluate the effectiveness of The Guide Cymru. All 205 secondary schools in Wales will be invited to take part, involving up to 30,000 year 9 pupils. Schools will be randomised to either the immediate implementation of The Guide Cymru or to a wait-list control. The wait-list control will receive The Guide Cymru around 12 weeks later. Measures of mental health literacy (assessed via the Knowledge and Attitudes to Mental Health scale) and mental health problems (via the PedsQL and Strengths and Difficulties Questionnaire) will be taken at baseline (pre-intervention), 12 weeks later (after the active group has received The Guide Cymru), and 24 weeks later (after the wait-list control has received The Guide Cymru).

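### The six-month SDQ recall is longer than the 12-week gap to wave 2, so the one untreated-control comparison of SDQ scores is diluted toward zero and a null result would be ambiguous

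*Protocol article*

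**What the plan says.** The protocol article lists the SDQ as a secondary outcome. Pupils answer its 25 items on a three-point scale "to indicate how far each item applies to the individual over the past 6 months". The section makes no provision for a shorter period at the repeat waves.

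The timing is fixed in several places:

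- The abstract sets the follow-up waves "12 weeks later (after the active group has received The Guide Cymru), and 24 weeks later".
- The Wave one section puts baseline "approximately 1 week prior to these teachers being trained on Go-To Educator".
- The Intervention section states: "These teachers will then deliver The Guide Cymru to their students over a next 8–10 weeks".
- The Wave two section sets testing 1–2 weeks "post the delivery of The Guide Cymru for the students in the intervention arm of the study".
- By wave 3 the wait-list schools have had the programme as well (Wave three; Secondary analyses).

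The neighbouring secondary outcome uses a shorter window. The PedsQL section says: "Participants rate each description regarding to their heath over the past month".

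The Primary analysis section compares the measures at waves 1 and 2. The Secondary analyses section says that PedsQL and SDQ data will be transformed for inferential testing, so the SDQ is not purely descriptive.

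**The concern.** The programme's effect is to be read from the change between waves 1 and 2, an interval of about 12 weeks. The SDQ asks about a period more than twice that long. A pupil who follows the instruction at wave 2 reports on many weeks that the programme could not have influenced, and many of those weeks were already covered by the wave 1 answer.

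A later wave cannot repair this, because wave 2 is the only follow-up at which the control arm is still untreated. The limitations section admits that follow-up is short but does not mention the recall period. A reader could therefore take a flat SDQ result as evidence that the programme does nothing for mental health difficulties, when the measure had limited ability to show a change.

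**Working it through.** **Inputs**

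- Recall window R: 6 months (SDQ section), taken as 26 weeks; 24 weeks is tried as well.
- Wave 2 at w = 12 weeks after baseline (abstract).
- Lessons start 1–2 weeks after baseline. Wave one gives about 1 week to the two-day training; the upper value allows one more week and is an assumption.
- Delivery takes 8–10 weeks (Intervention), and wave 2 follows 1–2 weeks later (Wave two).

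**Range for wave 2.** Adding the stages gives 1 + 8 + 1 = 10 weeks to 2 + 10 + 2 = 14 weeks, with the stated 12 in the middle.

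**Share of the wave 2 window before baseline** = (R − w)/R

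- w = 10: 16/26 = 62%
- w = 12: 14/26 = 54%
- w = 14: 12/26 = 46%
- R = 24, w = 12: 12/24 = 50%

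Two windows of length R that end w weeks apart share R − w weeks. The wave 1 and wave 2 windows therefore overlap by 14/26 = 54%. Waves 1 and 3 overlap by only (26 − 24)/26 = 8%, but both arms are treated by then.

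**Share before the first lesson** = (R − delivery − gap)/R. Delivery plus gap runs from 8 + 1 = 9 to 10 + 2 = 12 weeks. The share is therefore (26 − 9)/26 = 65% down to (26 − 12)/26 = 54%. With R = 24 it is 15/24 = 63% down to 12/24 = 50%.

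**Share after delivery ends.** SDQ: 1/26 = 4% to 2/26 = 8%. PedsQL, taking a month as 4 weeks: 1/4 = 25% to 2/4 = 50%, with the whole window after baseline.

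**Attenuation if pupils weigh the window evenly** (an assumption)

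- Full effect from the day after baseline: w/R = 12/26 = 46% (10/26 = 38% to 14/26 = 54% across the range for wave 2).
- Full effect from a first lesson at week 1: 11/26 = 42%.
- Effect building linearly over 10 weeks of lessons from week 1, then holding for one week: (0.5 × 10 + 1)/26 = 6/26 = 23%.

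**Power, as illustration only.** The plan's own figure reproduces. A standardised effect of 0.30, two-sided alpha 0.05 and 80% power give 175 per group. The design effect is 1 + (150 − 1) × 0.10 = 15.9, which the plan rounds to 16, and 175 × 16 = 2,800.

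The plan gives no effect size for the SDQ, so 0.30 is borrowed. Diluted, it becomes 0.30 × 0.423 = 0.13 or 0.30 × 0.231 = 0.07. Effective size per arm is n = N/15.9, and power is Φ(d√(n/2) − 1.96).

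- Predicted sample of 13,000, split equally: 6,500/15.9 = 409 per arm. Power falls from 99% to 44% or 17%.
- Required sample: 2,800/15.9 = 176 per arm. Power falls from 80% to 22% or 10%.

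Like the plan's own calculation, this takes no credit for precision gained from the baseline score.

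**The case against.** Several points on the other side are sound.

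- **No bias between arms.** Both arms answer over the same window, and yoked schools are tested on the same day in the same manner. What is lost is sensitivity.
- **A difference can still appear.** A reader might infer that the SDQ is unable to show an arm difference at wave 2. The document does not support that: 38–54% of the window lies after baseline, and a large enough effect would come through.
- **The SDQ does not stand alone.** A reader might also infer that it is the trial's only measure of mental health problems. The abstract assigns that role to the PedsQL and the SDQ together, and the PedsQL has emotional and social scales with a one-month window.
- **Even averaging is unproven.** Pupils of 13–14 may give recent weeks more weight, and the dilution would then be smaller. Nothing in the document settles this.
- **The SDQ carries little of the trial's case.** All six hypotheses concern mental health literacy. The Discussion also wants the mental health measures for relating literacy to mental health, a use that does not need a short window.
- **Changing the reference period alters an instrument** chosen for its documented psychometric properties.

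These points limit the consequence but do not remove the mismatch. The SDQ is listed as an outcome, is to be tested inferentially, and has a recall period longer than the interval over which change is measured. Admitting that follow-up is short does not cover this, because the recall period also weakens detection of an effect already present at wave 2.

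**Conclusion.** The point holds as a loss of sensitivity in one secondary outcome. On the stated schedule about 54% of the wave 2 SDQ window precedes baseline (46–62% for wave 2 at 14 to 10 weeks), and the wave 1 and wave 2 windows overlap by about 54%. If answers average evenly over the window, the SDQ arm difference at week 12 appears at no more than about 46% of its true size, and smaller if the effect builds up during delivery.

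The window shares rest on the document's own timings and on six months being about 26 weeks. The attenuation rests in addition on even averaging, and the power figures on a borrowed effect size.

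It would go too far to say that a null SDQ result would be caused by the recall window. Such a result would be ambiguous: it could reflect no effect, or an effect diluted below detection. The KAMH primary outcome, the sample size and the PedsQL are not touched. The matter should be put right, but it does not threaten the trial's main conclusion.

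**What to change.** Use an SDQ reference period no longer than the interval between waves, identical at all three waves and in both arms. One month would match the PedsQL. The change to the questionnaire is one line. The cost is that six-month norms, cut-offs and validation no longer apply directly; the between-arm comparison does not depend on the norms or cut-offs.

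If the six-month wording has to stay, treat the SDQ as a baseline descriptor or moderator. Add to the limitations that more than half of the wave 2 window precedes baseline on the planned schedule, and that a null wave 2 SDQ difference is not evidence of no effect. This costs nothing in data collection but gives up the SDQ as a test of the programme.

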### Statistical analysis

#### Descriptive statistics

Descriptive statistics for the samples (e.g., age, gender, socioeconomic status) will be provided. Mean scores (with standard deviations) will be calculated and presented for each of the three waves of evaluations.

#### Primary analysis

Multi-level modelling (MLM) will be used to test all hypotheses. Our primary analysis will compare the measures at wave 1 and wave 2. We expect to see time by group interactions, such that there are improvements in mental health literacy (e.g., knowledge score on KAMHs) from wave 1 to wave 2 for the treatment group but not for the wait list control.

#### Secondary analyses

We will examine the data from wave 3 to see if the treatment group has maintained its hypothesised increase in mental health literacy. We will examine if the wait list control (who will now have been administered The Guide Cymru) show a similar increase in mental health literacy and quality of life from their performance at wave 2.

We will examine factors that might moderate the effectiveness of The Guide Cymru, such as gender, Social Economic Status (SES) of the school, etc. by adding these into the MLM as a fixed factor and examining any significant interactions with these factors.

Pilot experiments have shown the data from the KAMH scales have an approximately normal distribution. Data from the PedsQL and SDQ are often positively skewed so medians and inter-quartile ranges will be presented, and the data will be transformed for the inferential statistical analyses.

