#### Statistical power

A power analysis was conducted to determine appropriate sample size. Our cluster size is determined by the number of secondary schools across Wales with there being approximately 205 schools in mainstream education with approximately 30,000 pupils in year 9 or around 150 pupils per school (though this cluster size will vary greatly across schools).

A normal (non-clustered) RCT power analysis with parameters of alpha = .05, power of 80%, and a standardised effect size of 0.30 (a small effect size for Cohen’s *d* and close to that obtained by [25] requires 175 pupils per group (*N* = 350). To account for the reduction in power due to clustering we assumed an average cluster size of 150, and an intra-cluster correlation coefficient (ICC) of 0.10, which leads to a design effect of 16 [25]. Hence, we require a sample size of around 2800 per group (*N* = 5600). Our predicted final sample size of 13,000 exceeds this (see Fig. 1) and allows a margin of error if our estimates of take-up or intra-cluster correlations are inaccurate.

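### Replication in the wait-list arm is judged by that arm's own wave 2 to wave 3 change, so any common time trend counts as programme effect; the contrast for maintenance is left open to the same bias

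*Protocol article*

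**What the plan says.** The primary analysis in the protocol article is controlled: a multi-level model with a group-by-time interaction over waves 1 and 2 (Primary analysis). Wave 3 belongs to Secondary analyses, which poses two questions.

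- **Maintenance:** "We will examine the data from wave 3 to see if the treatment group has maintained its hypothesised increase in mental health literacy". Only the treatment group is mentioned. No reference wave, comparator or test is given.
- **Replication:** whether the wait-list arm, by then trained, will "show a similar increase in mental health literacy and quality of life from their performance at wave 2". Here the reference is fixed: the same arm's own wave 2.

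Under Wave three, the wait-list schools are tested 1–2 weeks after their delivery, "with the yoked school in the active arm being tested at the same time", when the intervention schools are about 14 weeks past theirs. The Randomisation section also yokes the day of testing at every wave. Concurrent data on both randomised arms are therefore collected at wave 3.

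**The concern.** Once the wait-list arm has been treated, no untreated arm remains. Its change from wave 2 to wave 3 is the programme effect plus whatever would have happened anyway over those weeks: pupils get older, the school year moves on, other lessons touch on the subject, and the same questionnaire is sat for the third time. An upward drift would create or enlarge an apparent replication; a downward drift would hide a real one.

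If maintenance is also read from the intervention arm alone, an upward drift would mask fading. Wave 3 is the trial's only information on durability, and a large sample makes even a small drift likely to reach significance.

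**Working it through.** **1. The plan's own figure.** Inputs from Statistical power: "alpha = .05, power of 80%, and a standardised effect size of 0.30"; "requires 175 pupils per group"; "an average cluster size of 150, and an intra-cluster correlation coefficient (ICC) of 0.10, which leads to a design effect of 16"; "we require a sample size of around 2800 per group".

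- Unclustered: 2 × (1.960 + 0.842)² / 0.30² = 174.4, so 175 per group (two-sided).
- Design effect: 1 + (150 − 1) × 0.10 = 15.9, stated as 16.
- Clustered: 175 × 16 = 2800 per group.

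The stated figure reproduces and is not in dispute.

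**2. What each wave 3 quantity estimates.** Let e2 be the immediate effect in the intervention arm, m the effect it retains at wave 3, e3 the immediate effect in the wait-list arm, and t12 and t23 the common trends between waves.

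| Quantity | Estimates |
|---|---|
| Wait-list change, wave 2 to 3 | t23 + e3 |
| Intervention change, wave 1 to 3 | t12 + t23 + m |
| Between-arm difference at wave 2 (D2) | e2 |
| Between-arm difference at wave 3, intervention minus wait-list (D3) | m − e3 |
| Wave 2–3 change, wait-list minus intervention | e3 + (e2 − m) |
| D2 + D3 | e2 + m − e3, which is m only if e3 = e2 |

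Example with assumed values e2 = e3 = 0.30, m = 0, t12 = 0.1, t23 = 0.2 (SD units):

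- Wait-list change = 0.2 + 0.30 = 0.50, against a true 0.30.
- Intervention change, wave 1 to 3 = 0.1 + 0.2 + 0 = 0.30, which looks fully maintained although nothing is.
- D3 = 0 − 0.30 = −0.30, which shows the complete fading.
- Wave 2–3 difference in change = 0.30 + (0.30 − 0) = 0.60, so carrying the interaction forward mixes replication with decay.
- D2 + D3 = 0.30 − 0.30 = 0, the true retained effect.

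D3 has its own limit: m = e3 = 0.30 and m = e3 = 0 both give D3 = 0. The wave 3 data give two equations (t23 + e3 and m − e3) in three unknowns, so replication cannot be separated from trend without a further assumption.

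**3. How often drift alone would look like an effect.** Take the predicted sample ("Our predicted final sample size of 13,000 exceeds this"), equal allocation as the yoking implies, and the plan's design effect. Effective n per arm = 6500 / 15.9 = 408.8. With r the wave-to-wave correlation of an arm mean (assumed; not in the document), SE of within-arm change = √(2(1 − r) / 408.8). The chance of significance at two-sided 0.05 with no programme effect is Φ(drift/SE − 1.96), the other tail adding little.

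| r | SE | drift 0.05 SD | drift 0.10 SD |
|---|---|---|---|
| 0.5 | 0.049 | 17% | 52% |
| 0.7 | 0.038 | 26% | 74% |
| 0.9 | 0.022 | 62% | 99.5% |

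Cross-check from school level: 120 schools (Randomisation) give 60 per arm and 13,000/120 ≈ 108 pupils each. With ICC 0.10 and assumed correlations of 0.8 (school) and 0.6 (pupil), the variance of a school's mean change is 2 × 0.10 × 0.2 + 2 × 0.90 × 0.4/108 = 0.0467. SE = √(0.0467/60) = 0.028, and for 0.10 SD drift Φ(0.10/0.028 − 1.96) ≈ 0.95. This lies inside the range above.

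**4. Precision of the concurrent contrast.** A common trend cancels from D3. Its unadjusted SE is √(2/408.8) = 0.070 SD, a 95% half-width of 0.14. For D2 + D3, the unadjusted SE is 0.070 × √(2(1 + r)) = 0.12 to 0.14 SD for r = 0.5 to 0.9. Using wave 1 as baseline, with the same r between every pair of waves, it is 0.070 × √(2(1 − r)(1 + 2r)) = 0.099, 0.084 and 0.052 at r = 0.5, 0.7 and 0.9. That is at least twice the within-arm SE at each r.

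**The case against.** The strongest reply is that the article does not commit to a within-arm test of maintenance. It names no contrast, says multi-level models serve all hypotheses, and may leave the secondary model to a fuller document. That stands: a reader might infer that maintenance will be judged by uncontrolled change, but the text does not say so. It does not rescue the replication question, where the reference wave is written down.

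A reader might also infer that a free randomised comparison answers both questions and has been overlooked. The documents do not support that. At wave 3 the contrast is early-treated against late-treated, so alone it shows neither lasting benefit against no programme nor replication. Both uses in the fix need equal immediate effects in the two delivery periods.

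The wait-list arm's wave 1 to wave 2 change covers an untreated period of about equal length (waves at baseline, 12 and 24 weeks in the Abstract) and gives some view of drift. It is useful context, but it cannot remove seasonal or non-linear trends.

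Finally, these are secondary, exploratory questions, and no sentence commits the authors to a causal claim of lasting benefit. That limits the weight of the point without removing it.

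**Conclusion.** The point holds for replication as written: the wait-list change from wave 2 to wave 3 equals the programme effect plus any common trend. For maintenance it holds conditionally, if the question is read within arm. The false-positive range of 17% to 62% for 0.05 SD drift, and 52% to 99.5% for 0.10 SD, rests on assumed drift and correlations and on the plan's design effect. Nothing in the document shows that drift of either size will occur, so no single figure should be quoted. The randomised wave 1 to wave 2 comparison and the sample size are untouched. This is a worthwhile, inexpensive improvement to a secondary analysis, not a threat to the trial's main conclusion.

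**What to change.** Amend Secondary analyses as follows.

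1. Fit one three-wave multi-level model with a wave effect common to both arms, exposure states of not yet exposed, just completed and about 14 weeks after completion, and adjustment for geographic stratum.
2. Report the wave 3 between-arm difference with a confidence interval, as retained minus immediate effect (fading).
3. Report the retained effect against no programme as the wave 2 difference plus the wave 3 difference, also with an interval.
4. State that both readings assume the immediate effect is equal in the two delivery periods. The model then assumes replication and does not test it.
5. Label the wait-list wave 2 to wave 3 change as descriptive, show it beside that arm's untreated wave 1 to wave 2 change, and draw no causal conclusion from it.

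The cost is analysis wording only, with no new data. The price is the stated assumption and a larger standard error than for within-arm change.
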